Primary research questions include: 1) Is the intervention effective in increasing mothers’ likelihood of meeting breastfeeding and complementary feeding recommendations?; 2) Does the intervention improve responsive parenting/feeding behaviors?; 3) Is the intervention effective in decreasing children’s consumption of SSBs, snacks and desserts, and increasing consumption of age-appropriate fruits and vegetables?; 4) Is the intervention effective in increasing children’s physical activity levels and decreasing children’s screen time and other sedentary activities?; and 5) Does the intervention improve children’s BMI z-scores? Secondary research questions include: 1) Do maternal psychosocial factors and household food/water security and/or constrained PA environments moderate intervention impacts on: infant and young children’s feeding behaviors and infant and young children’s diets, PA patterns, and weight status?; 2) How do maternal/infant characteristics, diet, and behaviors impact the underlying biologic mechanisms of early childhood obesity?; and 3) Can social and behavioral interventions impact infant metabolic health?

The aim of this paper is to describe the Family Spirit Nurture intervention and the randomized controlled trial evaluating its efficacy.

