### Randomization

Participants are individually-randomized to receive the intervention or control program. Randomization is completed after the completion of the baseline assessment. Randomization is stratified by age (< 18 years old and 18 years and older), site, and food and water security status. Randomization lists for each site were created and uploaded to REDCap prior to study initiation using STATA 14 statistical software [61]. The randomization lists are not accessible by study staff. After baseline is complete, the field coordinator verifies baseline data and randomizes the participant in REDCap. Study staff are then informed of the participant’s study allocation. This is locked and unchangeable within REDCap.

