3 months post-partum	Early infancy 2 (biweekly)	• Play & communication activities • Looking/ smiling at child during feeding • Responding to baby’s cues and gestures • Establishing healthy sleep routines • Reducing exposure to screen time	• Promotion of exclusive breastfeeding (or formula feeding if breastfeeding not possible) • Gross & fine motor play • Continued tummy time • Monitoring patterns/ reducing screen time	• Skills for healthy living: handling stress, positive thinking, addressing home food, beverage, & PA environment
6 months post-partum	Mid-infancy (monthly)	• Play & communication activities (talking, singing, imitation) • Providing consistent routine • Eating with few distractions • Finger foods for child to touch	• Continued breastfeeding and/or formula feeding, along with complementary feeding (sequence) • Types/ textures of complementary foods • Increasing healthy diet variety • Gross & fine motor play	• Revisiting family planning/ sexual health (STI knowledge & testing) • Safe & reliable play spaces • Meal planning
9 months post-partum	Late infancy (monthly)	• Play & communication activities (“bye-bye”, imitation) • Singing to child during daily activities • Eating with child (modeling healthy eating) • Updating routines as needed	• Helping infant transition to healthy family lifestyle (diet & PA) • Ensuring infant is hungry at meals (avoid SSBs, snacks, desserts) • Continued breastfeeding and/or formula feeding	• Skills for healthy living: saying “no”, healthy relationships, problem-solving, positive thinking, accessing resources for a positive food & beverage environment
12 to 18 months post-partum	Toddlerhood (monthly)	• Monitoring toddler routines • Maintaining consistent routines (sleeping, eating) • Play & communication activities (reading, playing games) • Modeling healthy eating • Self-feeding • Avoiding food as a reward	• Giving toddler fixed “healthy” choices (e.g. banana or orange) • Transitioning to a cup • Dealing with food refusal and pickiness • Promoting PA/ reduced screen time • Involving toddler in food shopping & preparation • Providing daily opportunities for gross motor play	• Budgeting for family’s needs • Confident & effective parenting (consistent rules) • Toddler care practices/ making a safe home for play • Safe/ consistent alternative caregivers

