#### Lesson frequency and duration

FSN consists of 36 comprehensive lessons delivered bi-weekly from 28 weeks gestation until birth, weekly from birth to 3 months postpartum, bi-weekly from 3 to 6 months postpartum, and monthly from 6 to 18 months postpartum. Each visit is expected to take up to 60 min. Dosage is based on past evidence that effective home-visiting programs have generally planned for ~ 60 visits over a 1- to 5-year period and aimed to deliver between 32 and 56% of these visits (range 22–33 visits) [67]. Past Family Spirit trials established feasibility of proposed schedule [63].

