#### Primary outcomes

Group differences in percentage of mothers who meet breastfeeding and complementary feeding recommendations and percentage of mothers who introduce SSBs over time as assessed by the Child Feeding Assessment. From 2 weeks to 24 months pp., mothers are asked questions from an adapted version of the Pre-School-Aged Beverage Intake Questionnaire (BEVQ-15) in addition to items developed by the study team and based on previous studies conducted by the co-investigators. The assessment will be used to assess feeding practices, duration of exclusive and non-exclusive breastfeeding, timing of introduction of complementary foods and types of first foods, and introduction of SSBs.Group differences in mean scores for infant feeding style subscales assessed using the Infant Feeding Behavior Questionnaire, which asks mothers to indicate how often they engage in specific feeding behaviors to assess maternal feeding styles from 2 month to 12 months pp. There are five subscales that are used to assess maternal feeding style: Responsive, Forceful, Restrictive, Indulgent, and Uninvolved. There is no total scale score. The assessment is valid and reliable. This 24-item scale is scored with a 3-point Likert scale. A mean score is calculated for each subscale, with a range of 0 to 2. The range of the 3-point Likert scale is as follows: 0 (never), 1 (sometimes), 2 (always). Higher scores reflect higher levels of feeding style indicated by a given subscale.Group differences in in mean scores for toddler feeding style subscales assessed using the Toddler Feeding Behavior Questionnaire, which asks mothers to indicate how often they engage in specific feeding behaviors to assess maternal feeding styles at 24 months pp. There are five subscales that are used to assess maternal feeding style: Responsive, Forceful, Restrictive, Indulgent, and Uninvolved. There is no total scale score. The assessment is valid and reliable. This 27-item scale is scored with a 3-point Likert scale. A mean score is calculated for each subscale, with a range of 0 to 2. The range of the 3-point Likert scale is as follows: 0 (never), 1 (sometimes), 2 (always). Higher scores reflect higher levels of feeding style indicated by a given subscale.Group differences in children’s consumption of fruit and vegetable intake from SSBs, snacks, and desserts over time as assessed by the USDA Household Food Security Survey. From 6 months to 24 months pp., mothers are asked questions about her child’s fruit and vegetable consumption beginning at 6 months postpartum and at all subsequent time points. These items have been added to a standardized 18-item USDA food security survey, the U.S. Household Food Security Survey, that measures household food security. Fruit and vegetable consumption will be measured by asking mothers how much and how often her child eats fruits and vegetables and whether she feels she is able to provide her child with the fruits and vegetables he or she needs. To obtain weekly fruit and vegetable servings consumption, the number of times per week fruits or vegetables are consumed will be multiplied by the number of servings consumed each time. Serving size will be age adjusted.Group differences in children’s PA levels as assessed by accelerometry. At 18- and 24-months pp., children’s PA will be measured objectively using accelerometry. We will use the Actical accelerometer, a small waterproof device (28x27x10mm) weighing 17 g, which is omnidirectional (sensing motion in all planes) and integrates the degree and intensity of motion. We will use procedures co-investigators have used successfully in previous studies of young adolescents, toddlers and their mothers, placing the accelerometer on the non-dominant ankle with a non-removable, reinforced hospital band worn next to the skin, under socks, for 7 consecutive days. Accelerometers will be attached on the day of the 18- and 24-month assessment battery and removed one week later. Data will be collected in 1-min epochs. The time-stamped data will be examined. Summary statistics will include average and total activity counts and minutes in MVPA.Group differences in children’s reported PA, screen time and other sedentary activities over time as assessed by the Child Physical Activity Assessment from 2 months to 24 months pp. This 14-item self-report assessment includes questions about tummy time, crawling, walking, sedentary behavior and screen time for infants and toddlers. Questions were compiled based on a body of literature related to assessing infant/toddler physical activity.Group differences in children’s mean BMI z-scores over time (2 weeks to 24 months pp) as assessed through child weight and length measurements over time. Description: Child weight (to the nearest ounce) and recumbent length (to the nearest 1/8 in.) are measured using a digital scale and a recumbent measuring board (in accordance with IHS guidelines). All measurements will be taken in triplicate, removing the most disparate measurement, and averaging the remaining two. Averages will be used to calculate BMI z-scores using age- and sex-specific WHO Child Growth Standards.

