### Sample size calculation and statistical analysis

Sample size was powered to detect meaningful differences between the intervention (FSN + OSC) and control group (OSC + IPE) across six primary outcomes: 1) percent ever breastfed, 2) percent exclusively breastfed through 6 months of age, 3) mean duration of breastfeeding (at 12 months postpartum), 4) percent ever introduced sugar sweetened beverages at 12, 18 and 24 months, 5) mean score on responsive feeding scale (5-point scale – evaluated at 2, 4, 6, 9, 12, 18 and 24 months postpartum), and 6) mean BMI z-score at 24 months of age. A sample size of 338, or 169 per group, was deemed sufficient to detect meaningful differences across all outcomes, taking into account an estimated 16% loss-to-follow-up at 24 months postpartum (based on the previous FS trial) [54] and ensuring at least 80% power and significance level of 5%. Sample sizes and power were calculated using Stata 13’s power command (two means for continuous variables and two proportions for binary variables) (Table 3). The only exception among the primary outcomes was BMI z-score. Power simulation was conducted using a random draw and random treatment assignment from real site population data. The simulation varied the treatment effect and was run 10,000 times for each treatment effect level from which power was calculated. Simulation was also used to calculate power for moderator analyses. We hypothesize that maternal psychosocial factors, food/water insecurity and constrained physical activity environment will moderate the impact of the intervention on maternal feeding practices and healthy weight knowledge/behaviors. We also hypothesize that food/water insecurity and constrained physical activity could moderate the impact of improved maternal feeding practices and healthy weight behaviors on child diet and physical activity. While we will not have the power to examine interaction terms for all outcomes, we will have > 80% power to detect meaningful difference of differences in breastfeeding duration (48 days) and responsive feeding scales (0.4 to 0.6). The interaction terms for other outcomes will be explored as hypothesis generating to determine trends that would warrant further study with larger samples sizes.

**Table 3 Tab3:** Sample Size Calculations

Outcome Measures	Detectable Differences
% Mothers initiated breastfeeding	14%
% Exclusive breastfeeding through 6 months of age	15%
Mean breastfeeding duration	23 days

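### A constrained physical activity environment is hypothesised to moderate the FSN effect, but Table 2 names no measure of it before randomisation, and FSN itself aims to change it

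*Protocol article*

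**What the plan says.** The research questions at the end of Implementation of Family Spirit Nurture ask whether maternal psychosocial factors and "household food/water security and/or constrained PA environments moderate intervention impacts" on child feeding, diet, activity and weight status. Sample size calculation and statistical analysis turns this into a hypothesis. Alongside psychosocial factors, "food/water insecurity and constrained physical activity environment will moderate the impact of the intervention on maternal feeding practices". The same paragraph reports more than 80% power for a difference of differences of 48 days in breastfeeding duration and of 0.4 to 0.6 on the responsive feeding scales. It calls the interactions for other outcomes hypothesis generating.

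On timing, the Randomization section states: "Randomization is completed after the completion of the baseline assessment". The strata are age, "site, and food and water security status". FSN lessons are "delivered bi-weekly from 28 weeks gestation until birth".

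On content, the section Intervention: Family Spirit Nurture (FSN) lists constrained physical activity among the household factors that the programme is meant to address. Table 1 includes a block at 3 months on "addressing home food, beverage, & PA environment", a topic at 34 weeks gestation on making the home safe for play, and one at 6 months on play spaces.

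**The concern.** A treatment-by-moderator interaction compares the randomised arms within levels of a household characteristic. The comparison keeps the protection of randomisation only if that characteristic was fixed before treatment could act on it. If it is recorded later and FSN has changed it, the constrained FSN households are those FSN failed to relieve, whereas the constrained control households are all of those still constrained without FSN. The two groups are no longer alike, and the interaction no longer shows which families benefit more.

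The psychosocial and food/water moderators are also FSN targets, but their baseline values protect those tests. No equivalent protection is visible for the PA environment. At stake is one part of secondary research question 1: an effect of treatment on the home environment could be reported as moderation.

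**Working it through.** **Step 1. What precedes randomisation.** Because randomisation follows baseline, only the Baseline column of Table 2 counts.

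| Moderator group | Instruments with a baseline entry in Table 2 |
|---|---|
| Maternal psychosocial factors | Perceived Stress Scale, CESDR-10, ASSIST, Mastery Scale |
| Food and water security | Household Food Security Survey, Water Availability Assessment (also a stratification factor) |
| Constrained PA environment | None named or described as such |

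The other baseline entries are demographics, maternal beverage intake, the knowledge questionnaire, the injury assessment, and maternal height and weight. The knowledge questionnaire mentions physical activity in its title, but as knowledge of practices.

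**Step 2. The nearest instruments and when they start.**

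| Instrument | Time points in Table 2 | Content |
|---|---|---|
| Home Safety Environment Scan | 36 weeks gestation; 2 weeks; 9, 12, 24 months | Home safety |
| Child Physical Activity Assessment | 2, 4, 6, 9, 12, 18, 24 months | Child behaviour; itself a primary outcome |
| Current Eating Environment Assessment | 2, 6, 12, 24 months | Eating, not activity |
| Accelerometer | 18, 24 months | Child activity; itself a primary outcome |

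For the Child Physical Activity Assessment, Primary outcomes says: "This 14-item self-report assessment includes questions about tummy time, crawling, walking, sedentary behavior and screen time for infants and toddlers". That describes what the child does, not the setting.

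**Step 3. Order against the lessons.** FSN starts at 28 weeks and the earliest candidate is the 36-week scan. The 34-week topic on a home safe for play falls before that scan. The 3-month and 6-month topics fall after it and after the 2-month assessments, so they can affect only later measurements. Control mothers also receive a home safety topic, in lessons scheduled from 36 weeks onward. Later scans may therefore be influenced in both arms, by different content.

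**Step 4. The plan's own power figure.** Inputs are 169 per arm, 16% loss, 80% power, 5% significance (two-sided assumed) and the 23-day main effect in Table 3. The SD is not given, so it is solved from the 23 days.

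- Per arm: 169 × (1 − 0.16) = 141.96, about 142.
- Standardised detectable difference: (1.960 + 0.842) × √(2/142) = 0.332.
- Implied SD: 23 / 0.332 = about 69 days.
- For a binary moderator with prevalence p, the detectable interaction is 23 / √(p(1 − p)).

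| p | Detectable interaction (days) | Power for 48 days |
|---|---|---|
| 0.50 | 46.0 | 83% |
| 0.40 | 46.9 | 82% |
| 0.35 | 48.2 | 80% |
| 0.30 | 50.2 | 76% |
| 0.20 | 57.5 | 65% |

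At p = 0.50 the feeding-scale differences of 0.20 to 0.32 double to 0.40 to 0.64, against the stated 0.4 to 0.6. The article's figures are consistent with its inputs for a moderator of roughly 35% to 50% prevalence. What is missing is a variable to apply them to.

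**Step 5. Illustration of the bias, on assumed values only.** One million participants were simulated, with a 23-day treatment effect and no true interaction. A household factor shifted duration by 20 days per SD, the residual SD was 66 days, and half the homes were constrained at baseline. FSN moved some constrained homes to unconstrained, preferentially the better-placed ones.

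| Constrained FSN homes moved | Interaction, baseline moderator (days) | Interaction, later moderator (days) |
|---|---|---|
| 0% | 0.0 | 0.0 |
| 13% | 0.3 | −0.4 |
| 26% | 0.1 | −2.4 |
| 38% | −0.1 | −4.8 |

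The simulation error is about 69 × √(4/250,000) = 0.3 days, so the 13% row is close to noise. The last two rows are 2.4/48 = 5% and 4.8/48 = 10% of the detectable interaction. Size and sign depend on which households move, which the article cannot tell us.

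**The case against.** The strongest reply is that Table 2 lists titles, not items, and that titles in this trial do not fully reveal content: the child fruit and vegetable questions sit inside the food security survey. The 15-minute demographics interview, the knowledge questionnaire or the injury assessment could hold a usable baseline item, and a condensed article may leave the moderator's definition to the full protocol. This stands. A reader might infer that no participant has a baseline value, or that the test can only use a factor already changed by treatment. The documents do not support either inference. They show only that no such measure is named or described.

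It is also fair that the analyses are secondary. Primary aims analysis places moderators in secondary analyses, so calling this a confirmatory hypothesis would be wrong. The power sentence names two outcomes and no individual moderator. A reader might take it as a false claim about the PA environment, but its figures reproduce and it makes no specific claim about that factor.

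The article also has a second hypothesis, that constrained physical activity could alter how improved maternal practices translate into child diet and activity. The exposure there is itself measured after randomisation, so the present argument does not carry over directly. The point is confined to moderation of the intervention's impact.

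The objection does not remove the core. An analysis plan can choose a model or define a cut-point, but it cannot create a baseline value that was not collected.

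**Conclusion.** The point holds in a limited form. The article hypothesises moderation by a factor for which its list of measures shows no instrument before randomisation. Its nearest alternatives come after randomisation and possibly after the first lessons, and FSN is designed to change that factor. An interaction built on them would not be a clean test of moderation.

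The reach is one of three moderator groups within the secondary analyses. The primary comparisons, the sample size and the stated power figures are unaffected. The likely distortion is unknown. Under the assumed scenario it was modest, about 2 to 5 days against 48, so it would be too strong to say that the research question is unanswerable for this factor. The conclusion rests on reading instrument titles and descriptions, and a baseline item identified by the sponsor would resolve it.

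**What to change.** 1. State in Sample size calculation and statistical analysis that treatment-by-moderator interactions use only values collected before randomisation.
2. If an existing baseline questionnaire holds a PA-environment item, name it as the moderator.
3. If not, take this factor out of the hypothesis on moderation of intervention impact, say that the moderator power statement does not apply to it, and report it as exploratory or descriptive, or as a possible mediator.
4. Optionally, add a few PA-environment items to the baseline interview for mothers not yet enrolled. Recruitment is planned through Fall 2019, but the article does not say how many remain, so the sample would be partial and the interaction less precise.

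The cost is a change of wording and, if step 4 is taken, a little baseline interview time. The downside is that one secondary moderator hypothesis becomes exploratory.

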#### Primary aims analysis

We will conduct intent-to-treat analyses to estimate effects of the FSN + OSC intervention compared to the OSC + IPE control condition on early childhood obesity and related risk factors. Separately, we will examine the effects of intervention dose and conduct a “completer analyses” on subjects receiving minimum intervention dose (> 50% of lessons). Analyses will be adjusted for multiple comparisons using Bonferonni corrections.

Demographic and outcome variable distributions will be examined to assess whether comparability between intervention groups at baseline was achieved through randomization. For time discrete outcome measures, t- tests or chi-square tests will be used to test whether the intervention impacted each outcome in unadjusted analyses. Multiple linear or logistic regression will be used to test the impact of the intervention on each outcome, controlling for baseline demographic characteristics where necessary and examining potential moderators in secondary analyses. For time varying outcome measures we will examine the impact of the intervention by analyzing between group differences at each time point using t-tests and multiple regression analyses. For those outcomes with sufficient power, multi-level mixed-effects regression with a random effect at the individual level and appropriate variance structures, and an interaction term for treatment x child age will be used to examine change over the course of the intervention period for the intervention and control groups.

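### Bonferroni is promised with no stated divisor over primary outcomes that expand to about 27 or 42 comparisons, while the trial is sized at an unadjusted 5%

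*Protocol article*

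**What the plan says.** Primary aims analysis makes two commitments. On multiplicity: "Analyses will be adjusted for multiple comparisons using Bonferonni corrections". On repeated measurements: "For time varying outcome measures we will examine the impact of the intervention by analyzing between group differences at each time point", by t-tests and multiple regression. A mixed model with a treatment-by-age term is added for outcomes judged to have enough power. It is not said to replace the visit-by-visit tests.

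Sample size calculation and statistical analysis sizes the trial "across six primary outcomes", "ensuring at least 80% power and significance level of 5" per cent. Two of the six are not single comparisons:

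- One is "percent ever introduced sugar sweetened beverages at 12, 18 and 24 months".
- The other is the responsive feeding scale, "evaluated at 2, 4, 6, 9, 12, 18 and 24 months postpartum". Table 3 gives a separate detectable difference for each of its subscales.

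Primary outcomes says of that scale: "There are five subscales that are used to assess maternal feeding style: Responsive, Forceful, Restrictive, Indulgent, and Uninvolved. There is no total scale score". Table 2 schedules the infant version at 2, 6 and 12 months and the toddler version at 24 months, so four visits rather than seven.

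Primary outcomes also lists items that are not among the six: complementary feeding recommendations, fruit and vegetable intake, accelerometry, and reported activity and screen time. It defines BMI z-score over time, whereas the sample size section takes it at 24 months.

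**The concern.** A Bonferroni rule means something only once the set of comparisons is fixed. Here the article gives two primary lists, two visit schedules for the feeding scale, five subscales of equal standing, and several models per outcome. It does not say what the correction divides by.

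The choice can decide the result. A p-value of 0.005 for BMI z-score at 24 months would be positive against 0.05/6 = 0.0083 and negative against 0.05/27 = 0.0019.

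The choice also trades one fault for another. A small divisor applied to many tests may not hold the 5% error rate. A divisor that matches all the tests takes away most of the power for the obesity endpoint, and 20 of the 27 shares of alpha go to one questionnaire. Neither outcome fits a sample size justified at an uncorrected 5%.

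**Working it through.** **Inputs.** From the sample size section: 169 per arm, 16% loss, 5% significance, 80% power, six outcomes. From Table 3: 0.33 SD for BMI z-score. From Table 2: four feeding-scale visits. From Primary outcomes: five subscales, no total. Two-sided testing is assumed because the article does not state sidedness. Correlations between tests are not given, so they are assumed and shown as a range.

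**1. Reproduce the plan's figure.** Evaluable per arm: 169 × (1 − 0.16) = 142. Noncentrality: 0.33 × √(142/2) = 2.781. Normal approximation at two-sided 5%: Φ(2.781 − 1.960) = 79.4%; with the t distribution, 79.1%. The article obtained its BMI figure by simulation, but 0.33 SD at 80% power is reproduced, and the alpha behind it is an undivided 5%.

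**2. Count the comparisons.**

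| Outcome | Table 2 visits | Sample size section's visits |
|---|---|---|
| Ever breastfed | 1 | 1 |
| Exclusive breastfeeding to 6 months | 1 | 1 |
| Breastfeeding duration | 1 | 1 |
| SSB introduction, three ages | 3 | 3 |
| Feeding scale, five subscales | 5 × 4 = 20 | 5 × 7 = 35 |
| BMI z-score at 24 months | 1 | 1 |
| Total | 27 | 42 |

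Testing BMI z-score at all eight Table 2 visits adds 7. With one SSB age and one feeding visit the count is 3 + 1 + 5 + 1 = 10.

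**3. Family-wise error if the divisor is six.** For m independent tests it is 1 − (1 − 0.05/6)^m. For equicorrelated normal statistics it is found by numerical integration.

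| Tests | Independent | ρ = 0.5 | ρ = 0.8 |
|---|---|---|---|
| 10 | 8.0% | 6.2% | 3.7% |
| 27 | 20.2% | 12.4% | 5.9% |
| 42 | 29.6% | 16.3% | 7.1% |

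At ρ = 0.9 the 27-test figure is 3.7%, so the excess over 5% depends on the correlation. With 0.05/27 for 27 tests the error is at most 5% (4.9% if independent).

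**4. Power for 0.33 SD in BMI z-score, 142 per arm.** Normal approximation: Φ(2.781 − z). Detectable difference at 80% power: (z + 0.842) × √(2/142), where √(2/142) = 0.1187.

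| Alpha | z | Power, normal | Power, t | Detectable difference (SD) |
|---|---|---|---|---|
| 0.05 | 1.960 | 79.4% | 79.1% | 0.33 |
| 0.05/6 | 2.638 | 55.7% | 55.0% | 0.41 |
| 0.05/27 | 3.113 | 37.0% | 36.1% | 0.47 |
| 0.05/42 | 3.241 | 32.3% | 31.3% | 0.48 |

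**The case against.** The strongest reply is that the article never divides by six. Bonferroni ordinarily divides by the number of comparisons made, and on that reading the error rate is controlled. The exact family and the deciding model are also details that an article commonly leaves to the full protocol or SAP, neither of which is shown. Both statements are right, and they rule out several stronger readings that a reader might infer:

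- **That the plan leaves an inflated error rate of a particular size, such as 11–18%.** That needs both a divisor of six and a moderate correlation, and the article gives neither.
- **That 27 is a minimum.** It follows from testing every listed subscale and visit. One contrast per outcome with five subscales gives 10, and a mixed model could stand in for the visit-by-visit tests.
- **That the feeding scale alone would give a false primary success more than twice as often as 5%.** At 0.05/6 its 20 tests give 15.4% if independent and 10.2% at ρ = 0.5, but 6.9% at ρ = 0.7 and 5.2% at ρ = 0.8.
- **That the divisor will be chosen after the data are seen.** The article does not show this.

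The reply does not remove the conflict among the things the article does state. It commits to testing at each visit, to five subscales with no total, to a Bonferroni correction and to 80% power at 5%. Reading the divisor generously solves the error rate only by giving up the stated power. The two outcome lists and the two feeding schedules also disagree within the article, so a later SAP would have to depart from one of them.

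**Conclusion.** The concern holds as an inconsistency between the multiplicity rule, the outcome definitions and the sample size. It does not hold as a demonstrated error rate.

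The firmest part is power. Any Bonferroni divisor of six or more takes BMI z-score power for 0.33 SD from about 79% to about 55% or lower, and to about 36% at a divisor of 27. This rests on 142 evaluable children per arm, two-sided tests and the article's own 0.33 SD.

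The family-wise error is conditional. With a divisor of six and 27 tests it is about 6% to 20% for an assumed common correlation between 0.8 and 0. With a divisor of 27 it is controlled.

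This is worth correcting before unblinding, because a borderline primary result can change sign with the divisor.

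**What to change.** 1. Reconcile the primary outcome list under Primary outcomes with the six in the sample size section, including whether BMI z-score is judged at 24 months or over time. Do not adopt the six by default, since that would silently drop declared primary outcomes.
2. Reconcile the feeding-scale visits in the sample size section with Table 2.
3. Before unblinding, name one deciding contrast for each primary outcome: one subscale where there are several, one age, one model. Which subscale and which age is the investigators' choice.
4. Apply Holm instead of Bonferroni across exactly that set at two-sided 5%. It controls the same error rate and is never less powerful. With six contrasts its first step is 0.05/6, so BMI power lies between about 55% and 79%, depending on how many of the other contrasts are rejected.
5. Label the remaining subscales, visits and models supportive, with no confirmatory claim.
6. Restate power or detectable differences in Table 3 at the adjusted level.

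**Cost.** No new data are needed. The other subscales and visits lose confirmatory status, and the stated power becomes less favourable. By the article's own Ethical considerations section, a protocol modification goes to the relevant IRBs as an amendment, so this is more than an editorial change.
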